### **7.3.2 Termination of the Study**

The Sponsor reserves the right to prematurely discontinue the study at any time. If the study is terminated or suspended, the sponsor and/or its designees will promptly inform the investigators/institutions and regulatory authorities. The IRB/EC should promptly be informed and provided the reasons(s) for the termination or suspension by the investigator/sponsor, as specified by the applicable regulatory requirement(s).

Reasons for terminating the study may include the following:

- The incidence or severity of AEs in this study indicates a potential health hazard to study subjects
- Subject enrolment is unsatisfactory,
- Data recording is inaccurate or incomplete.

The Sponsor may terminate the study at a study site when the investigator fails to comply with relevant regulations or insufficiently adheres to protocol requirements or recruitment remains insufficient (as deemed so by the sponsor).

## **8. STUDY TREATMENTS**

### **8.1 Study Treatment**

The study treatment under evaluation is Rhenium-SCT.

#### **8.1.1 Treatments Administered**

Rhenium-SCT (50Gy dose at target depth) will be administered on Day 0, as a single treatment, by application on a protective foil applied over the area to be treated, such that the radioactive material does not come into contact with the subject. The depth of lesion is determined before treatment by Histology (biopsy).

The lesion is marked out prior to treatment with a 5mm safety margin. The irradiation time required to achieve the desired target dose at the defined penetration depth is calculated based on the amount of radioactivity of the substance being applied, the surface area to be treated and the depth of the lesion. The dose at target depth, the deepest point of the lesion, is defined as 50Gy. This dose, also known as target dose, aims for mortality of tumorous cells at the target depth. After the calculated irradiation time has elapsed, the Rhenium-SCT is removed by pulling the foil from the skin. A full user guide will be provided to the site.

OncoBeta makes a program available to the sites that allows them to verify their calculations. After introducing the input values (lesion size, depth and activity applied), the program will calculate the treatment time needed for each individual lesion, based on the given dose, considered at the deepest point of the lesion (dose at target depth).

This program, which is intended to support the physicists with the patient's dose assessment, is based on VARSKIN 5 calculations, a well-known software used to calculate dose to the skin resulting from exposure to radiation. VARSKIN 5 uses dose point kernels (DPK) that are Monte Carlo based and the code agrees with the EGSnrc Monte Carlo code. User manual will be provided.

Validation of the delivered dose was performed via phantom-based experiments.

The (recommended) dose at target depth used by the software, 50Gy, is based on [name] work, which is also part of the medical device certification process. 50Gy is the dose approved as part of the CE certification.

The target dose is set to 50Gy. The treatment time will be determined based on the size and depth of the area needed to treat, and the activity applied to it. If a layer is painted thicker on one subject, that would be translated into a higher activity applied, recorded by the dose calibrator, and a reduced treatment time.

#### **8.1.2 Identity of Investigational Products**

Rhenium-SCT is obtained from a 188W/188Re generator and has a half-life of about 17 hours, which means that it decays continuously over a short period of time. Rhenium-SCT Molecules produced from the elution of the 188W/188Re generator are bound to a fluid matrix resulting in the compound inside the carpoules. The Rhenium-SCT isotope used for the Rhenium-SCT treatment is a Beta-emitter with main decay energies of maximum 2120 keV with 71% intensity

and 1965 keV with 25% intensity (765 keV on average). In addition to its main Beta-emissions, Rhenium-SCT emits  $\gamma$ -radiation of 155 keV with a 15% intensity, as well as other Beta- and  $\gamma$ -emissions of different energies. Instructions for device preparation can be found in the Rhenium-SCT Technical Dossier.

### 8.1.3 Packaging and Labelling

Rhenium-SCT Carpoules will be supplied by the Sponsor including a CE compliance certificate, or Therapeutic Goods Administration Australia (TGA) compliance certificate.

Rhenium-SCT Carpoules filled with radioactive compound (medical device part, reference number 0300) will be supplied by the Sponsor, including a CE (Conformité Européenne) compliance certificate, or Therapeutic Goods Administration Australia (TGA) compliance certificate. The medical device part will be labelled according to CE mark and ISO14155:2020

The Base Station, Applicator and Measurement Station include the following information in their labelling:

- Serial Number (SN)
- Item Number or Reference Number (REF)
- Year of manufacture
- Manufacturer information

The SN is presented in the form of CCC-NN (CCC = 3-digit batch, NN = 2-digit serial device number within a batch)

For each of the radioactive carpoules, the following information is included in the labelling:

- Serial number
- Date of manufacture
- LOT number
- Activity
- Calibration date and time
- Expiry date
- Position within the transport unit
- Manufacturer information and sponsor information (if applicable)

On the day of the therapy, together with the carpoules, the clinics will receive subject documentation labels with the above-mentioned information for each of the carpoules received (see image of label below).

[figure not shown]

**Patient documentation label**

Prior to the therapy, the clinics will also receive the Certificate of Compliance (CoC) for the goods, which gives the treating physician a summary of what will be received (template attached):

- LOT/Charge number
- Summary of the carpoules inside the package, with their SN and the activity and mass at the calibration time
- Manufacturer information
- Information about the radionuclide
- Manufacture, calibration and expiry dates

With this document OncoBeta officially confirm that the carpoules received comply with the specification and that we approve its use with patients.

Additional labels accompany the goods, but the ones mentioned above can be used for traceability purposes given that they will be received by the clinics and can be used for their records.

Rhenium-188 compound is filled inside a single-use plastic container, hereinafter referred as carpoules. One carpoule is filled with approx. 300 mg of the rhenium-188 compound and has a maximum activity of 2,2 GBq at the beginning of the treatment. The content of a carpoule is sufficient for the treatment of an area of up to 25 cm^2 and it can be used to treat several lesions and subjects depending on the sizes of the lesions. The therapeutic range of Rhenium-188 beta radiation in unshielded human tissue is about 2-3 mm (92% of the dose is delivered within the first 3 mm).

The carpoules are transported to the treatment centre inside a certified type A package consisting of an inner 35 mm lead container and a big aluminium outer box, considerably reducing the emitting dose. Dose rate limits at the outer surface of the lead container at its maximum loading capacity (around 50 GBq) would be 3 mSv/h and 30 µSv/h at 1 m distance separation. NOTE: the maximum loading capacity is considered at the end of the production before they are shipped to the treatment centre.

#### **8.1.4 Handling and Storage**

Details on preparation and administration of the Rhenium-188 compound are provided in the Rhenium-SCT Instructions for use. Rhenium-SCT compound is filled inside the single-use Carpoule, which is the active therapeutic product used to treat subjects (Figure 1). Rhenium-SCT is applied over the area to be treated (tumour or lesion including safety margin) on a protective foil, such that the radioactive material does not come into contact with the subject.

**Figure 1. Rhenium-SCT Carpoule**[figure not shown]

Rhenium-SCT can be applied in any radiation control area with a suitable license for handling Rhenium-188 open sources. The license must cover sufficient annual and daily activity based on the frequency of treatments. A license with annual activity of approximately 500 GBq is recommended for a weekly treatment plan.

Since radiation control areas tend to be limited in space, it is very possible that two or more subjects could be treated simultaneously with the Rhenium-SCT in the same room. The treatment room should have enough treatment beds/chairs for the subjects. Subjects should be placed at least 1.2 m away from each other in order to protect them from cross radiation. Accordingly, the treatment beds/chairs should be positioned in a way that the treated lesions are at least 1.2 m away from the walls of the room, if the material and thickness of the walls are unknown.

The shielding for the room walls must be calculated by a physicist, considering an average specific activity of 100 MBq/cm^2. Due to the weak penetration of the beta emission a minimum of 10 cm concrete wall (outer and inner walls alike) is enough to stop the radiation emitted by the compound. In a worst-case scenario, the radiation burden for a subject due to another subject sitting 1.2m away is negligible and estimated to be around 1.17 µSv. The use of a plastic or lead screen can be used in the unlikely case that two subjects must sit close together and at least one lesion faces the other subject. A few millimetres of plastic (3.5 mm) will drop the dose by >90%.

Treatment will only be conducted at facilities with appropriate radiation licencing.

### **8.1.5 Compliance and Accountability**

The Investigator, designated pharmacist, or radiology personnel will acknowledge receipt of the shipment and note content and condition of the shipment on the clinical material shipping form.

Treatment centres need to have a defined waste management system. Disposals, consisting of empty or unused carpoules, protective foils with Rhenium-188 compound on them and any other radioactive waste, will be disposed of separately over a period of 2-3 weeks for the Rhenium-188 to cool down. The exact waiting time before disposal of the waste depends on the total delivered REC activity and it must be calculated by a physicist. After this period, the

materials can be disposed as non-radioactive waste. If the facility does not have means for the waste management, OncoBeta GmbH can provide special waste containers for this purpose. These waste containers have a 15 mm lead wall and can hold up to 22.5 GBq.

Radiation waste is to be managed as per site Radiation Management Plan.

#### **8.1.6 Prior and Concomitant Therapy**

Prior: Other relevant previous medication as judged by the investigator should be documented in the eCRF. Note that subjects who have had surgery and/or radiation therapy for the target lesions are excluded from the study.

Concomitant: concomitant medications should be kept to a minimum during the study. However, if these are considered necessary for the subject's welfare and are unlikely to interfere with the study objectives, they may be allowed at the discretion of the investigator. Only relevant associated concomitant medications, as deemed appropriate by the investigator, are to be recorded in the eCRF (as deemed appropriate by the investigator).

#### **8.1.7 Unacceptable/Prohibited Therapy**

All treatments that the investigator considers necessary for a subject's welfare may be administered at the discretion of the investigator in keeping with the community standards of medical care.

Subjects may receive other medications that the investigator deems to be medically necessary.

There are no prohibited therapies during the post-treatment follow-up phase. It is however advised that no topical treatments be applied to the treated lesions for approximately 4 weeks following treatment with Rhenium-SCT.

It is left to investigator discretion if subjects are asked to cease therapy with radio sensitising agents before and after Rhenium-SCT treatment. This can be recorded as concomitant medication in the eCRF.

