## **6. STUDY DESIGN**

### **6.1 Overall Study Design**

This is a prospective, multicentre, single arm, open-label, phase IV/ Post Marketing Clinical Follow-up (PMCF), study consisting of:

- A screening period of up to 30 days duration, to ensure that the subject is eligible for the study
- A follow-up period of 24 months. Each subject will remain in the study for 24 months from the time of their treatment with Rhenium-SCT. Subjects requiring further or alternative treatments for the target lesions during the trial period, will leave the study.

The study is completed with the last visit of last subject.

Details on all study visits can be found in the time and events schedule in Section 9.

An interim analysis is planned once 50% of subjects have recorded a 6-month follow-up visit.

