## 7.2 Exclusion Criteria

A subject will not be eligible for inclusion if any of the following criteria applies during screening or prior to enrolment:

1. Inability to personally provide written informed consent or to understand and collaborate throughout the study
2. Inability or unwillingness to comply with study requirements
3. Prior treatment with surgery or radiation therapy for their target lesion(s)
4. Depth of lesion greater than 3mm as defined by Biopsy and/or clinical assessment
5. Lupus and Scleroderma
6. Basal cell naevus syndrome, xeroderma, vitiligo and albinism
7. Prior laser at the tumour site
8. Malignant melanoma systemic therapy ongoing
9. Any ongoing treatment for malignancy, or in the last 4 weeks prior to study entry
10. A tumour affecting nerves or bony structures
11. Clinical concern of metastatic disease
12. Pregnancy and/or lactation
13. Pathological exclusions: Perineural Invasion, Lymphovascular invasion
14. Anatomical exclusions: NMSC's of the Medial canthus, eyelid margin (upper and lower), Vermillion lip
15. Participation in another clinical trial or administration of any investigational product or experimental product within 60 days prior to screening.

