| Histology****                                                  | X                   |                                     |                                       |                                        |                                                                          |                                        |                            |                            |                                                       |                        |
| Informed consent                                               | X                   |                                     |                                       |                                        |                                                                          |                                        |                            |                            |                                                       |                        |
| Demographics                                                   |                     | X                                   |                                       |                                        |                                                                          |                                        |                            |                            |                                                       |                        |
| Medical history                                                |                     | X                                   |                                       |                                        |                                                                          |                                        |                            |                            |                                                       |                        |
| Concomitant medications                                        |                     | X                                   | X                                     | X                                      |                                                                          |                                        | X                          | X                          |                                                       |                        |

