#### **12 month follow up visit:**

- Photography of treated lesions (medical photographer or site digital camera)
- CTCAE grading
- Quality of Life questionnaire completed via trial App (or on paper during the visit if subject does not have a smart phone)
- Cosmetic outcome; subject rated. To be completed on Trial app (or directly into the eCRF if the subject does not have a smart phone). VAS image found in the protocol appendix 3
- Cosmetic outcome: Clinician rated. To be completed into the eCRF using VAS in the protocol appendix 3
- Modified Visual RECIST assessment. Guide to assessment is found in protocol appendix 5
- Histology to be performed if lesion is visible, suspected or if this is the site's regular clinical practice

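### Section 8.1.7 does not fit 8.1.6 or the exit rules, and no scheduled item after month 6 asks about therapy that could affect a treated site

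*Protocol*

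**What the plan says.** Four parts of the protocol bear on therapy after Day 0.

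- **Permission.** Section 8.1.7 says "There are no prohibited therapies during the post-treatment follow-up phase" and adds "It is however advised that no topical treatments be applied to the treated lesions for approximately 4 weeks following treatment with Rhenium-SCT". The second sentence is advice and has an end date. Section 8.1.6 sets a condition on concomitant medications: "if these are considered necessary for the subject's welfare and are unlikely to interfere with the study objectives, they may be allowed", at the investigator's discretion.
- **Exit.** Section 6.1 says "Subjects requiring further or alternative treatments for the target lesions during the trial period, will leave the study". Section 7.3.1 requires withdrawal when the same lesion is retreated with another therapy or device, and has the date, circumstances and reason entered on the eCRF withdrawal page. Section 9.1.4 repeats the exit rule, but refers to the subject's lesions without limiting this to target lesions.
- **Recording.** Section 8.1.6 says "Only relevant associated concomitant medications, as deemed appropriate by the investigator, are to be recorded in the eCRF". The Table 2 row "Concomitant medications" is marked at baseline, Day 0, the 14-day visit, 3 months and 6 months. It is blank at 12 and 24 months, and the visit lists in 9.1.3 agree. No row or list covers local procedures at a treated site.
- **Entry.** Exclusion 9 in section 7.2 covers "Any ongoing treatment for malignancy, or in the last 4 weeks prior to study entry". It does not reach past entry.

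**The concern.** In a single-arm, open-label trial there is no control group in which other therapy would act equally. Attributing a response to one application of Rhenium-SCT depends on knowing what else reached the lesion. Two things weaken that here.

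First, the sections give a site different answers on the same event. A topical field treatment started in month 2 could be acceptable under 8.1.7, doubtful under 8.1.6, and an exit event under 6.1 or 7.3.1 if it is judged to be treatment of the target lesion.

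Second, the schedule stops asking about concomitant medication at 6 months, while response is assessed again at 12 and 24 months and cosmetic outcome is rated only then. A lesion cleared by therapy given for another reason could be counted as a response to the device. A cosmetic procedure at the site could raise the VAS score. The situation is foreseeable, because inclusion criterion 3 admits subjects with more than three lesions.

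**Working it through.** **Step 1: which therapies the exit rules catch.**

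- Therapy given openly for a target lesion: 6.1 and 7.3.1 apply, the subject leaves and the reason is recorded. This route is closed.
- Field or systemic therapy given for another lesion or condition that also acts on a treated site: not retreatment of the same lesion under 7.3.1. Section 8.1.7 permits it, 8.1.6 may not, and 9.1.4 can be read either way. Recording is at the investigator's discretion.
- Scar or cosmetic treatment of the site: not treatment of the tumour, so no exit is triggered.

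**Step 2: where the schedule asks (Table 2 and 9.1.3).**

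| Visit | Concomitant medications | Response | Cosmetic VAS |
|---|---|---|---|
| 3 months | yes | no | no |
| 6 months | yes | yes | no |
| 12 months | no | yes | yes |
| 24 months | no | yes | yes |

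**Step 3: which lesions this can affect.** The analysed endpoint is best overall response (section 11.7), taken up to 24 months (Appendix 5). A lesion in CR at 6 months keeps CR as its best response, so for that endpoint later therapy matters mainly for lesions not in CR at 6 months. Section 9.2.1 also states a CR rate at 12 months. For that figure, therapy that hides a recurrence after month 6 would count too.

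**Step 4: the plan's own sample-size statement.** Section 11.1 gives n = 120, one-sided alpha 0.025 and at least 80% power for the pairs in Table 3. I use the exact binomial test and treat each value in the left column as the threshold p0. The critical count r is the smallest with P(X ≥ r | 120, p0) ≤ 0.025, and power is P(X ≥ r | 120, p1).

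| p0 / p1 | r | Exact alpha | Power |
|---|---|---|---|
| 85% / 94% | 110 | 0.022 | 0.893 |
| 86% / 94% | 111 | 0.021 | 0.816 |
| 87% / 95% | 112 | 0.020 | 0.853 |
| 88% / 96% | 113 | 0.019 | 0.891 |
| 89% / 97% | 114 | 0.018 | 0.930 |
| 90% / 97% | 115 | 0.016 | 0.847 |

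The statement is reproduced, and this point does not affect the sample size.

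**Step 5: sensitivity to conversion by other therapy.** Assume that the device alone gives a CR rate exactly equal to p0, and that a share m of the remaining lesions becomes CR through other, unrecorded therapy in subjects who stay on study. The protocol gives no value for m. The observed rate is p = p0 + (1 − p0)m, and the chance of a false conclusion is P(X ≥ r | 120, p). For p0 = 0.88 and m = 0.10: p = 0.88 + 0.12 × 0.10 = 0.892, and P(X ≥ 113) = 0.046.

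| p0 (r) | m = 0 | 10% | 20% | 30% | 50% |
|---|---|---|---|---|---|
| 85% (110) | 0.022 | 0.057 | 0.134 | 0.274 | 0.711 |
| 88% (113) | 0.019 | 0.046 | 0.101 | 0.201 | 0.568 |
| 90% (115) | 0.016 | 0.036 | 0.075 | 0.148 | 0.442 |

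The expected number of converted lesions is 120 × (1 − p0) × m. At m = 10% this is 1.8 at 85% (120 × 0.15 × 0.10) and 1.2 at 90% (120 × 0.10 × 0.10). At m = 20% it is 3.6 and 2.4.

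**The case against.** The strongest reply is that the protocol already deals with the main case. A topical antineoplastic applied to a residual target lesion is another therapy for the same lesion, so 7.3.1 requires withdrawal with a recorded reason. It would also fail the condition in 8.1.6. Lesions in CR at 6 months cannot gain from later therapy on best overall response. Site photographs continue to 24 months, App photographs are reviewed monthly up to 12 months, monitors compare the eCRF with medical records, and 8.1.6 does not confine recording to scheduled visits.

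Most of this stands. A reader might infer that CR and cosmetic results can come from other therapy with no means of detection. The documents do not support that, because openly given retreatment leads to exit and is documented.

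A reader might also note that 109 CRs of 120 (exact lower 95% limit 84.2%) meet none of the six thresholds, while 115 (90.5%) meet all six, and conclude that a few unrecorded treatments could decide the trial. The arithmetic is right. But the step from 109 to 115 needs 6 of the 11 failures (6/11 = 55%) to be cleared by unrecorded therapy in subjects who remain on study, and nothing in the protocol suggests a share that high.

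The safeguards do not reliably reach therapy given under another label. The App photographs are not scored. Adverse events after 30 days are collected only if treatment-related. Histology at 12 months is conditional: "Histology to be performed if lesion is visible, suspected or if this is the site's regular clinical practice". Recording of medication depends on the investigator finding it relevant.

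**Conclusion.** The point holds in a limited form. Section 8.1.7 is inconsistent with 8.1.6 and with the exit rules in 6.1, 7.3.1 and 9.1.4, and these passages must be reconciled. After the 6-month visit no scheduled item asks about field, systemic or cosmetic therapy affecting a treated site, although 12- and 24-month response and both cosmetic ratings come later.

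Any effect on CR is towards success, since conversions can only add CRs. Its size is unknown. Under the assumptions in Step 5, conversion of 10% of non-CR lesions raises the chance of a false non-inferiority conclusion from 0.016-0.022 to 0.036-0.057, and conversion of 20% raises it to 0.075-0.134. No figure can be put on the cosmetic effect from the documents.

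This is a worthwhile, inexpensive improvement and not a defect that undermines the primary result. It belongs in the protocol because an analysis plan cannot recover data that were never collected.

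**What to change.** 1. Add concomitant medications and local procedures at treated sites to the 12- and 24-month columns of Table 2 and to the matching visit lists in 9.1.3. Make recording compulsory for any antineoplastic, field-directed or cosmetic treatment at or near a treated site and for any systemic anticancer agent.
2. Reconcile 8.1.6, 8.1.7, 6.1, 7.3.1 and 9.1.4 so that a site can tell which therapy at a target lesion is an exit event. Which therapies to allow is a clinical decision for the sponsor and investigators, and none is proposed here.
3. Report CR and cosmetic results with and without lesions exposed to such therapy. The detail can sit in the statistical analysis plan.

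The cost is one short eCRF item at two visits that already take place, plus wording changes. The reported CR rate may be slightly lower. No visit is added and no subject's care is restricted.
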